## Study Sites and Patient Enrolment:

- - 1. *Clinics:* The study will be conducted using 22 clinics which have previously been used for ACT Consortium research. Twelve clinics are situated in Nanagahar Province (East Region) and ten clinics are based in Kunduz Province (North Region). The study areas have varying malaria endemicity, with higher incidence in the East Region. All clinics have been included as study sites for the previous phases of the project and are included in this study as a representative sample of typical clinics in different malaria endemic areas. The clinics are all primary care clinics (Basic Health Centre or Comprehensive Health Centre). They are staffed by a clinic doctor, who acts as the manager, and other staff (for example, nurses or midwives) who occasionally run the clinic when the doctor is away from post. Each centre also has a community health supervisor, who is responsible for the community health workers attached to each clinic.

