### Trial Arms:

**Phase I:**

*Arm 1: Non-intervention arm:*

The non-intervention arm will be based on the existing clinical diagnosis, pre-referral treatment and referral to a clinic in areas where RDTs have not been deployed at CHW level. Arm 1 CHWs will receive refresher training according to the National Strategy for CBMM which includes the current IMCI guidelines.

Vs:

*Arm 2: RDT Arm*

Provision of community level diagnostics by rolling out RDTs to CHWs through the national strategy for Community based Management of Malaria. The arm has been designed exactly as the current National guidelines for RDT implementation..The arm will include:

- Clinic level microscopy or RDT and CHWs using RDTs to provide parasitological diagnosis to diagnose, treat and/or refer patients. Under this scheme, CHWs will be provided with CQ, SP and artesunate (AS). Depending on the diagnostic result, they prescribe according to the National Treatment Guidelines (CQ for confirmed vivax, SP and AS for confirmed falciparum, and no antimalarial for a negative result).
- CHW training will be conducted exactly as described in the CBMM strategy, using a “trickle down approach” where Training of Trainers takes place at the central level for provincial trainers of local NGOS who run the health service. These, in turn, run workshops for training CHSs and CHWs (see section 2.2 for pre-evaluation of training and roll-out). Participants will receive training to enforce revised IMCI guidelines, taken from the CBMM strategy document, which include an RDT in the algorithm for fever (see annex 2).
- There are no plans for additional support or refresher training, and no plans for quality control and assurance contained in the National Plan.
- CHWs are not equipped with suitable storage facilities for the RDTs, for example evaporative coolers.
- Monitoring and evaluation takes place according to the draft strategy.

The second phase of the trial will be initiated in Feb 2012. The second phase of the trial will re-randomise clinics to either the RDT arm (as in arm 2, above) and a third arm (arm 3). The third arm will answer the question: “how can the performance of RDTs at community level be enhanced?”. The same set of outcomes will be used to measure the relative effectiveness of each approach. A revised random allocation using the same methods will be conducted for the Phase II randomisation.

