### Trial Secondary Outcomes:

- % of Pf cases treated with ACT.
- % of patients <10 years of age who are correctly treated (estimated at 40% of all patients)
- % of malaria negative patients receiving antimalarial drug
- % of malaria negative patients receiving antibiotics
- % of patients treated per policy

Per policy defined as:

- Suspected malaria which is PCR confirmed treated with CQ/SP
- Community based diagnosed Pf, subsequently confirmed as Pf treated with SP/AS
- Community based diagnosed Pv, subsequently confirmed as Pv treated with CQ
- No antimalarial given to negative cases (confirmed by PCR)
- Proportion of patients incorrectly treated in each arm, including data collected at the clinic level.
- Time to first treatment from onset of symptoms.
- Cost per patient correctly treated.
- Cost per patient treated per policy.
- Invalid rate, specificity and sensitivity of RDTs deployed at community level (against PCR).
- Number of patients attended by CHWs and type of attendance.
- Number and proportion of patients successfully referred by CHWs to BHCs.
- Proportion of malaria negative and positive given antibiotics at CHW and/or clinic level.

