### Risks and potential adverse events:

There are minimal risks associated with this study. Blood samples would, in most cases, be taken anyway for the application of the RDT is associated with minimal risk of secondary infection at the puncture site and with mild pain.

The main risk is in the mistreatment of falciparum malaria with either no antimalarial or with an ineffective antimalarial (i.e. CQ). Currently, falciparum malaria is quite rare in the study areas (although it may vary seasonally and geographically) so the risk of this occurrence is low. According to the National Guidelines and the study protocol, all Pf positive patients will be referred to a clinic for further evaluation which further reduces the risk of this occurring, since all clinics will have parasitological diagnosis available (either through RDT or through microscopy).

The trial intervention arm is unlikely to increase this risk, in fact, rather the opposite. This potential adverse event will be monitored throughout the trial and its occurrence will be reported to the Data Safety and Monitoring Board (DSMB). Immediately following a PCR result which is positive for Pf (regardless of coinfection), results from the patient record form will be cross checked to see which treatment was given. Because of logistical constraints, PCR results will not be known for more than 2 weeks after the initial assessment of the patient. Every effort will be made to trace the patient and ensure that they have recovered. If not, they will be referred to the health facility for further treatment.

Depending on the frequency with which this event occurs, the study staff will inform the DSMB of any action being taken which could include re-training of staff or withdrawal of CHWs from the trial. All efforts will be made to follow-up the patient within a few days of knowing the PCR result. All patients will be advised by CHWs to seek treatment at the clinic if symptoms recur or continue following the treatment.

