| 10 | Proportion of malaria cases confirmed by RDT in targeted Health Posts | **Numerator:** Number of reported malaria cases confirmed by RDT in targeted BHCs, HSCs and Health Posts  **Denominator:** All reported malaria cases from targeted BHCs, HSCs and Health Posts | Included in the evaluation.  The denominators will be (a) the number of suspected malaria cases (fever) and (b) the number of PCR confirmed malaria cases.  Draft Target: 85% |
| 11 | Proportion of reported falciparum cases confirmed by RDT treated with ACTs in targeted BHCs and HSCs | **Numerator:** Number of reported falciparum cases confirmed by RDT treated with ACTs in targeted BHCs and HSCs  **Denominator:** All reported falciparum cases confirmed by RDT from targeted BHCs and HSCs | Included in the evaluation.  The denominators will be (a) the number of suspected malaria cases (fever) and (b) the number of PCR confirmed malaria cases.  Draft Target (taken from national malaria strategic plan): 90% |
| 12 | Proportion of reported falciparum cases confirmed by RDT treated with ACTs in targeted Health Posts | **Numerator:** Number of reported falciparum cases confirmed by RDT treated with ACTs in targeted BHCs, HSCs and Health Posts  **Denominator:** All reported falciparum cases confirmed by RDT from targeted BHCs, HSCs and Health Posts | Included in the evaluation.  The denominators will be (a) the number of suspected malaria cases (fever) and (b) the number of PCR confirmed malaria cases.  Draft Target (taken from national malaria strategic plan): 90% |
| 13 | Proportion of reported non-falciparum cases confirmed by RDT treated with chloroquine + primaquine in targeted BHCs and HSCs | **Numerator:** Number of reportd non-falciparum cases confirmed by RDT treated with chloroquine + primaquine in targeted BHCs and HSCs  **Denominator:** All reported non-falciparum cases confirmed by RDT from targeted BHCs and HSCs | Included in the evaluation.  The denominators will be (a) the number of suspected malaria cases (fever) and (b) the number of PCR confirmed malaria cases.  Draft Target (taken from national malaria strategic plan): 90% |

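### Indicators 11 and 13 in the Arm 2 evaluation count only RDT-confirmed cases at BHCs and HSCs over denominators with no test, facility or species limit, so the results are biased down against the 90% target

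*Protocol*

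**What the plan says.** Section 2.6 (Outcomes) announces an interim evaluation of the RDT arm, and section 2.6.3 sends the reader to Annex 3 for its indicators. There the investigators sorted the national list. Indicators 11 and 13 are among those kept, each with a draft target of 90%.

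- Indicator 11 is titled "Proportion of reported falciparum cases confirmed by RDT treated with ACTs in targeted BHCs and HSCs", and its numerator is "Number of reported falciparum cases confirmed by RDT treated with ACTs in targeted BHCs and HSCs".
- The numerator of indicator 13 is restricted in the same way, to non-falciparum "cases confirmed by RDT treated with chloroquine + primaquine in targeted BHCs and HSCs".
- The investigators' note on both changes only the denominators: "The denominators will be (a) the number of suspected malaria cases (fever) and (b) the number of PCR confirmed malaria cases".

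On the clinics themselves, section 2.2 says: "The clinics are all primary care clinics (Basic Health Centre or Comprehensive Health Centre". Section 2.4 stratifies an interview subgroup by CHC versus BHC. No study clinic is described as an HSC. The Arm 2 definition in section 2.5.1 begins with "Clinic level microscopy or RDT and CHWs using RDTs to provide parasitological diagnosis", and section 2.10.3 says that "all clinics will have parasitological diagnosis available (either through RDT or through microscopy". Section D of the clinic form (Annex 5) has separate entries for a slide result and an RDT result.

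Section 2.6.2 also lists as a secondary outcome: "Number and proportion of patients successfully referred by CHWs to BHCs".

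**The concern.** A proportion set against a target should be able to reach that target when performance is perfect. Under the national denominators, which are themselves limited to RDT-confirmed cases at BHCs and HSCs, a CHC patient or a slide-only patient lies outside the indicator and does no harm. The investigators' denominators carry no limit on facility, test or species, while the numerators keep theirs. A PCR-positive patient seen at a CHC, or diagnosed by slide only, then counts in the denominator and cannot count in the numerator, however well treated.

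The clinic result would then partly measure which test and facility type served the patient. A shortfall from 90% could be read as poor treatment when it is produced by the definition.

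**Working it through.** There is no stated figure to reproduce, because the point rests on definitions. The check has two steps.

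**1. Who can be counted**

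| | Facility | Test | Species |
|---|---|---|---|
| Numerator, indicator 11 | BHC, HSC | RDT | falciparum |
| Numerator, indicator 13 | BHC, HSC | RDT | non-falciparum |
| Denominator (a), suspected cases | no limit | no limit | no limit |
| Denominator (b), PCR-confirmed cases | no limit | no limit | no limit |
| Study clinics (2.2, 2.5.1, 2.10.3) | BHC, CHC | microscopy or RDT | all |

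Sections 2.7.1 and 2.9.4 provide for blood spots at clinic level and from all enrolled patients, so CHC and slide-only patients do reach denominator (b).

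**2. Highest attainable value with perfect treatment**

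Inputs:
- s = share of clinic malaria cases seen at a CHC or diagnosed by slide only. The protocol does not give it; 0 to 75% is assumed for illustration.
- f = falciparum share of malaria cases, about 5-10% (section 1.2), assumed to apply to clinic cases.
- Every case in the numerator is assumed to be PCR-confirmed, s is assumed equal across species, and mixed infections are ignored.

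Formulas:
- Species-matched PCR denominator: ceiling = 1 - s, for both indicators.
- Denominator (b) as written: ceiling = (1 - s) × f for indicator 11, and (1 - s) × (1 - f) for indicator 13.

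| s (assumed) | Species-matched, 11 and 13 | Indicator 11, (b) as written | Indicator 13, (b) as written |
|---|---|---|---|
| 0% | 100% | 5-10% | 90-95% |
| 5% | 95% | 4.75-9.5% | 85.5-90.25% |
| 10% | 90% | 4.5-9% | 81-85.5% |
| 20% | 80% | 4-8% | 72-76% |
| 50% | 50% | 2.5-5% | 45-47.5% |
| 75% | 25% | 1.25-2.5% | 22.5-23.75% |

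With species matching, 1 - s falls below 0.90 once s exceeds 0.10. If the 11 Arm 2 clinics of Phase I carried equal weight, one fully excluded clinic would give 1 - 1/11 = 90.9% and two would give 1 - 2/11 = 81.8%.

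With (b) as written, indicator 11 is capped at 5-10% even when s = 0. Species mixing is therefore the larger defect for that indicator. Opening the numerator to all clinics and both tests, with (b) unchanged, only returns to the s = 0 row: 5-10% for indicator 11 and 90-95% for indicator 13. Denominator (a) can only be larger, since it adds suspected patients without malaria, so its ceilings are lower still.

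**The case against.** The strongest reply is that these are benchmarks and not trial outcomes. Annex 3 reproduces a national draft, section 2.6.3 warns that the indicators may change, and keeping national wording for comparison with a national target is defensible. That stands as a reason to report the national version as well. It does not defend the version actually specified, whose denominators already depart from the national ones.

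A second reply is that the note may intend its denominators to be restricted to the facilities, test and species named in each indicator. That is possible, and the ceilings would then disappear. The note does not say so, however, and gives the same denominators for every indicator kept.

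A third is that s may be small. Annex 3 assumes plentiful RDTs at the clinics when it drops the stockout indicators. This stands as a caution on size. It does not remove microscopy from the Arm 2 definition, bring CHCs into the numerator or touch the species problem.

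Three stronger inferences are not supported:
- A reader might infer that CHC and slide-only patients can never count as correctly treated in the trial. Section 2.6.1 defines correct treatment against PCR with no condition on test or facility, and the clinic-level outcome in section 2.6.2 is separate from Annex 3.
- A reader might infer a distortion by province from the new microscopy centres in Kunduz (section 1.1). The protocol does not say which study clinics gained microscopy.
- A reader might infer that the referral outcome misses every referral to a CHC and is biased between arms. The facility term there is probably shorthand: elsewhere referral is simply to a clinic, and the Annex 5 item on referral by a CHW does not depend on clinic type.

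**Conclusion.** The point holds for indicators 11 and 13 as written. Numerator and denominator differ in facility, test and species, and the resulting bias against the 90% target is downward. For indicator 11 with denominator (b), the ceiling is about 5-10%, resting on the protocol's own falciparum share. With species matched, the ceiling is 1 - s. Because s is not given, the figures for it are illustrative and show only that a share above 10% puts the target out of reach.

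The consequence is confined to these benchmarks. The primary outcome and the clinic-level treatment outcome are not affected. The referral wording in section 2.6.2 is a minor alignment.

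**What to change.** In the notes to indicators 11 and 13, define numerator and denominator on the same basis:

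- **Facilities:** all study clinics, BHC and CHC.
- **Diagnostic basis:** the clinic's own RDT or slide result as recorded in Annex 5 section D, with results also shown by test type.
- **Species:** PCR-confirmed falciparum for indicator 11 and PCR-confirmed non-falciparum for indicator 13.

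Report the original national version alongside for comparison with the target. If denominator (a) is kept, present it descriptively and not against 90%, since suspected cases cannot be matched on species. With both sides aligned and the PCR denominator species-matched, the ceiling is 100% and the target becomes attainable.

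As a minor alignment, let the referral outcome in section 2.6.2 refer to a study clinic (BHC or CHC).

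The cost is wording only. The clinic form already records slide result, RDT result and referral by a CHW, and PCR is planned for all enrolled patients. The small downside is that the main version departs from the national wording, which the parallel national version offsets.

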## Annex 4: CHW Data collection form – this page is the front, and next page is the reverse of the form.

[figure not shown]

[figure not shown]

## Annex 5: Clinic Patient Tracking Form:

**A. Patient details:** (Study registrar – please fill out this section)

(Attach the patient ID sticker)

**1. Patient ID number:**

**2. CRT Patient ID Card Number: None (not enrolled)**  **Yes**  **-** **CRT ID:**

**3. Was the Patient Referred: No**  **Yes, referred by CHW**  **by other clinic**

**by family member**

**by other**

**4. Did the patient consult a CHW before attending the clinic:**

**No**  **Yes**  *- Which CHW (write name and village):*

CHW Name: Village:

**5. Patient name:**

**6. Sex: Male**  **Female**

**7. Age:** [  ][  ] **years**

**8. Date of Visit:** [  ][  ] - [  ][  ] - **1390** (Persian format: DD-MM-YYYY)

**9. Reference sample: Blood spot**  **(please tick √ when collected)**

**B. Clinician details:** (Clinician – please write your name & mark your job title/position in the box below)

**1. Name of clinician:**

**2. Position of clinician: MD (**♂**)**  **MD (**♀**)**  **Nurse**  **CHS**  **Midwife**

**C. Patient history & clinical exam:** (Clinician - please write patient signs and symptoms in this box)

**1. _______________________________________________________________________**

**2. _______________________________________________________________________**

**D. Clinic Diagnosis result:** (Clinic microscopist – please record the slide results in this box)

**No Laboratory Diagnosis:**

**Clinic slide result: *P. falciparum***  ***P. vivax***  **Mixed**  **Negative**

**RDT result:**

**F. Clinician’s diagnosis:** (Clinician - please write all the final diagnoses for the patient in this box)

**1. _______________________________________________________________________**

**2. _______________________________________________________________________**

**G. Prescription:** (Clinician – please write the patient’s full prescription in the box below)

**Anti-malarial**  **Antipyretics**  **Antibiotics**  **Other**

**Patient name: _________________________________ Date: ___________________**

**1. _______________________________________________________________________**

**2. _______________________________________________________________________**
